## Abstract

**Background:**

Depression and anxiety are common among pregnant women. Internet-delivered psychological therapies such as cognitive behavioral therapy (iCBT) have been developed to increase accessibility and address common help-seeking barriers, especially during pandemic period. The objective of this trial is to evaluate the short-term and long-term effects of iCBT on reducing depressive symptoms among pregnant women during the COVID-19 pandemic with the overall goal of preventing depression recurrence in the first 12 months postpartum.

**Methods:**

A multi-site randomized controlled trial will be conducted where 300 pregnant women early in their third trimester will be screened for depression symptoms using the Edinburgh Postnatal Depression Scale (EPDS) during a routine obstetrical visit. Eligible and consenting women with a score greater than 9 will be randomly allocated (1:1) to either intervention group or control group. ICBT involving the completion of 7 weekly online modules will be delivered via a well-designed perinatal mental healthcare app. The primary objective is to evaluate the effect of iCBT on reducing depression symptoms among pregnant Chinese women starting from their third trimester. The secondary objectives are to examine the effect of iCBT on anxiety, sleep quality, social support, parenting stress, co-parenting relationship, and infant development.

**Discussion:**

This multi-center randomized controlled trial has been planned in accordance with best practices in behavioral trial design. The internet-based intervention addressed the needs of pregnant women during a major pandemic where face-to-face therapy is not preferable. The trial has a relatively large sample size with sufficient power to evaluate the efficacy of iCBT intervention for the primary and secondary outcomes. One year follow-up evaluation in the study is designed to determine the longer-term effect of the intervention on both maternal and infant outcomes. Although a limitation is the assessment of depression and anxiety using self-report measures, these easily incorporated and maternal-preferred assessments allow for real-life scalability if the intervention is proven to be effective.

**Ethics and dissemination:**

Ethics was approved by the institutional review board of International Peace Maternity and Child Health Hospital (GKLW2020-25). Dissemination of results will be published in peer-reviewed academic journals and presented at scientific conferences.

**Trial status:**

The first patient was enrolled on 19 August 2020. To date, 203 participants have met eligibility requirements and been randomized to either the intervention group or control group. Data collection aims to be complete in September 2022. Date and version identifier: 2020715-version1.0.

**Trial registration:**

ChiCTR2000033433. Registered 31 May 2020, http://www.chictr.org.cn/showproj.aspx?proj=54482.

**Supplementary Information:**

The online version contains supplementary material available at 10.1186/s13063-022-06728-5.

## Introduction

Large-scale infectious diseases are known to have adverse psychological effects on both the general population and specific vulnerable subgroups [1–4]. During the coronavirus disease 2019 (COVID-19) pandemic, frequently reported concerns such as fear of infection, social isolation, stigmatization, discrimination, unemployment, and financial loss have resulted in a significant increase in mental illness rates among women and younger populations [5]. In a cohort study spanning China, pregnant women after the declaration of COVID-19 human-to-human transmission in China were significantly more likely to have depression and thoughts of self-harm than pregnant women before the pandemic [6].

Maternal depression and anxiety are the most common psychiatric disorders that develop during pregnancy and postpartum [7]. Although reports of mental illness related to the perinatal period date back to the middle ages, the management of this global public health issue remains suboptimal. Postpartum depression prevalence rates vary among countries, ranging from 6.9 to 12.9% in high-income countries to more than 20% in some low- or middle-income countries [8]. Whether the incidence of depression peaks postnatally is questionable given research showing that 33% of women with depression actually developed symptoms during pregnancy [9]. Anxiety is equally common as depression postnatally with meta-analytic data suggesting 15% of women have high levels of anxiety across the first year postpartum and that 9% of women develop comorbid depression and anxiety. The strongest risk factor for postpartum depression or anxiety is a history of a mental illness, especially during pregnancy. Most depression or anxiety episodes resolve within a few months of treatment, but one in four women diagnosed with depression are still symptomatic at one year postpartum and about 40% will relapse [10]. Importantly, antenatal depression is associated with adverse pregnancy outcomes including elective or emergency cesarean section, preterm birth, and small for gestational age [11–14]. It is also well documented that postpartum depression has consequences for the mother and her family with broader negative effects related to work, caregiving, and society as well. Moreover, one particular concern is the influence of maternal depression on parenting behaviors, which results in increased risk of poor maternal-child attachment and, in the longer term, impaired emotional, social, and cognitive development [15] including internalizing and externalizing psychopathology [16].

Although the far reaching adverse effects of perinatal mental illness is internationally recognized, it surprisingly continues to be under-treated. In many countries, perinatal mental health services in antenatal care remain limited due to women’s reluctance to report changes in their mood [17] and provider barriers such as lack of time, limited knowledge, and cost/insurance mismatch [18]. During the COVID-19 epidemic, there is an even greater need for perinatal mental health services including the provision of easily accessible preventive and treatment interventions [19, 20].

Psychological therapies are the first-line treatment recommended for adults with mild to moderate depression [21]. Cognitive behavioral therapy (CBT) is a practical, short-term form of psychotherapy where individuals learn to identify, question, and change the thoughts, attitudes, and beliefs related to the negative emotional and behavioral reactions. It is a highly effective depression treatment among the general population and perinatal women [22]. Moreover, internet-based programs have been developed to increase accessibility and address common help-seeking barriers [23]. While evidence for the effectiveness of iCBT on the treatment of depression is encouraging [24], not all studies have demonstrated an improvement in symptomatology compared to inactive controls [25]. There is also evidence showing that CBT can be initiated in pregnancy for the prevention of postpartum depression [26]; however, no studies have examined the effect of iCBT on women at high risks of antenatal depression during a large-scale infectious diseases outbreak where limited medical resources are provided. To meet the urgent need for reliable access to effective depression interventions during the COVID-19 outbreak and to develop a new collaborative initiative between the departments of obstetrics and psychiatry in China, the purpose of the proposed trial is to evaluate the effect of iCBT on treating depression symptoms among pregnant women with the aim of preventing postpartum depression.

### Study objectives

The primary objective of this study is to evaluate the effect of iCBT on reducing depression symptoms among pregnant women in their third trimester with the aim of preventing depression across the postpartum period assessed using the Patient Health Questionnaire 9-item scale (PHQ-9) [27]. The secondary objectives are to evaluate the effect of iCBT on (1) anxiety using the Generalized Anxiety Disorder (GAD-7) [28], (2) sleep quality using the Pittsburgh Sleep Quality Index (PSQI) [29], (3) social support using the Multidimensional Scale of Perceived Social Support (MSPSS) [30], (4) parenting stress using Parenting Stress Index-Short Form (PSI-SF) [31], (5) co-parenting relationship using the Brief Co-parenting Relationship Scale (BCRS) [32], and (6) infant development using the Denver Development Screen Test (DDST) [33].

## Methods and analysis

### Study design

The study is a multi-center, superiority, randomized controlled trial of two parallel groups that adheres to CONSORT guidelines [34]. Figure 1 depicts a flow diagram of the study design.

**Fig. 1 Fig1:**
[figure not shown]
Flowchart of the study design

### Study setting

Pregnant women will be recruited through obstetric clinics at the International Peace Maternity and Child Health Hospital in Shanghai China and other four cooperative medical centers from different regions in China including (1) Hunan Maternal and Child Health Care Hospital in Changsha, Hunan; (2) Women’s Hospital affiliated with Zhejiang University School of Medicine in Hangzhou, Zhejiang Province; (3) Hanghzhou Women’s Hospital in Hangzhou, Zhejiang Province; and (4) Shaoxing Maternity and Child Health Care Hospital in Shaoxing, Zhejiang Province.

### Participant eligibility

#### Inclusion criteria

All pregnant women are eligible to participate if they meet the following inclusion criteria: (1) singleton pregnancy; (2) ≥ 28 weeks gestation; (3) 18 years of age or older; (4) able to read and understand Chinese; (5) has an Edinburgh Postnatal Depression (EPDS) [35] score > 9; and (6) has reliable internet access via a smartphone or computer.

#### Exclusion criteria

Exclusion criteria include (1) active suicidal ideation, (2) severe psychopathology (e.g., schizophrenia), and (3) currently receiving treatment for depression and anxiety including other psychotherapy or medication.

### Procedure

The study procedure is described by following the Standard Protocol Items: Recommendations for Interventional Trials (SPIRIT) checklist (Supplementary Material).

#### Participant screening, recruitment, and enrolment

All pregnant women will be assessed with EPDS by a trained research assistant during their standard antenatal visit between 28 and 34 weeks gestation. Those with an EPDS > 9 will be introduced to the study and provided with a detailed study explanation. Eligible women agreeing to participate will complete informed consent procedures and will be financially compensated when they finished the trial. Following the completion of a baseline questionnaire, women will be randomized to either the control group (standard care for women with antenatal depressive symptoms) or the intervention group (standard care for women with antenatal depressive symptoms plus access to iCBT).

#### Randomization and blinding

Following the collection of baseline data, eligible women will be allocated in 1:1 ratio to either the intervention group or control group by the research assistant using a computer-generated block randomization procedure provided by the Clinical Research Public Technical Service Platform (http://www.scrcnet.org/CRIS_en.asp#top). The allocation sequence will be implemented by using a web-based central randomization system. Participants will then be assigned to either the intervention group or the control group according to the results of the computer-generated randomization system. Due to the nature of the intervention, health care professionals providing iCBT intervention will not be blinded to group allocation but participants will be. Follow-up questionnaires will be completed confidentially online by participants and depression scores will be reviewed by a trained research assistant not involved in other trial activities. Safety protocols used in previous trials completed by team members will be followed for participants who score positively to self-harm ideation.

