#### Intervention

The iCBT intervention will be provided via personal devices connected to the internet or mobile network. A perinatal mental healthcare app has been designed for participants to receive text or video-based psychoeducational modules published weekly for 7 weeks by a trained therapist (Fig. 2). Three modules will be delivered antenatally, and four will be provided postnatally available until 5 weeks after delivery. Weekly modules include psychoeducation, self-monitoring logs and outcome monitoring. Written feedback from participants to the therapist via the app is also required after each module is published. Consistent with well-established CBT theory and protocols [36, 37], the main component of iCBT includes mental health education, cognitive reconstruction, problem solving strategies, behavior reinforcement, and relapse prevention. Table 1 shows the schedule of seven-week period iCBT intervention. The app records metrics that can be used to evaluate adherence or engagement, including completion of modules and recording logs, and duration of time spent in the online system. The study team will have access to the weekly activity logs and be aware of adherence to online modules. Participants will receive an automatic reminder message via the app as well as personal contact from the therapist if they have not engaged with the weekly module material or provided feedback.

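### The protocol says participants are blinded, but the arms it describes make that impossible, and those participants rate the primary outcome themselves

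*Protocol article*

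**What the plan says.** The Randomization and blinding section of the protocol article attributes the lack of provider blinding to the nature of the intervention and then claims the opposite for the women: "health care professionals providing iCBT intervention will not be blinded to group allocation but participants will be".

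Other sections describe what the women experience:

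- **Screening, recruitment and enrolment.** Women who screen positive are "introduced to the study and provided with a detailed study explanation", give consent, and are randomized to standard care alone or to "standard care for women with antenatal depressive symptoms plus access to iCBT".
- **Intervention.** The iCBT arm receives "psychoeducational modules published weekly for 7 weeks by a trained therapist", with self-monitoring logs and obligatory written feedback to the therapist. A woman who falls behind gets an app reminder and "personal contact from the therapist if they have not engaged with the weekly module material or provided feedback".
- **Usual care control.** Both arms share educational videos and mental health assessment, including PHQ-9 and GAD-7 through the app at 6 weeks postpartum.
- **Primary outcome measure.** Prevalence of depression at 6 weeks postpartum on the PHQ-9, described as a self-report instrument. On collection: "Follow-up questionnaires will be completed confidentially online by participants". An assistant with no other role in the trial reviews the depression scores.
- **Data management.** The biostatistician is blinded to allocation.
- **Abstract, Discussion.** Self-report of depression and anxiety is named as a limitation, without reference to knowledge of allocation.

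**The concern.** A woman who works through therapist-published modules, hands in assignments and writes to a therapist knows that she is receiving iCBT. A woman who was told about the study and is offered none of this can infer that she is not. The reason given for not blinding providers applies equally to recipients.

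This matters because the participant is also the outcome assessor. Participant blinding is the safeguard that would guard a self-rated PHQ-9 against reporting that depends on allocation. The protocol claims that safeguard, and the design does not have it. The Implications section says positive results would be strong evidence of effectiveness. A reader who accepts the blinding sentence would give too little weight to reporting and expectation effects when judging that evidence.

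**Working it through.** The main check is a comparison of statements. The arithmetic only shows what the correction does and does not touch.

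**1. Could the described arms be masked?** Masking participants would need at least one of the following:

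- *Similar content in the control arm.* Not described. The shared videos cover labor and delivery, postpartum self-care, infant care and breastfeeding. Modules, assignments and therapist feedback are described for iCBT only.
- *Concealment of the hypothesis or of what the arms contain.* Not described. Women receive a detailed explanation before consent.
- *No visible mark of allocation.* Ruled out by the required feedback and the therapist's personal contact.

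**2. Does any other safeguard blind the rating?** The order of events is: the participant completes the PHQ-9 online, an assistant reviews the score, the biostatistician analyses it. The second and third steps come after the rating and cannot blind it.

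**3. Does the correction change a design figure?** Inputs from the sample size section: 47.3% versus 22.2%, 90% power, two-sided 0.05, 20% loss. With unpooled variance:

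n = (1.960 + 1.282)² × [0.473 × 0.527 + 0.222 × 0.778] / (0.473 − 0.222)² = 10.507 × (0.2493 + 0.1727) / 0.0630 = 70.4, so 71 per arm.

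71 / (1 − 0.20) = 88.75, so 89 per group and 178 in total, as stated. Blinding status does not enter the formula, so nothing here changes.

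**4. Illustration, on assumptions that are not in the document.** Suppose no true effect, a control rate of 47.3%, and 120 analysed per arm (300 × 0.80 / 2). Suppose further that knowing the allocation shifts reporting in the iCBT arm on a latent normal scale. The threshold is c = Φ⁻¹(1 − 0.473) = 0.068, and the shifted rate is 1 − Φ(c + shift).

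| Assumed shift | iCBT rate | Apparent reduction | Chance of two-sided p < 0.05 |
|---|---|---|---|
| 0.1 SD | 0.433 | 4.0 points | about 9% |
| 0.2 SD | 0.394 | 7.9 points | about 23% |
| 0.3 SD | 0.357 | 11.6 points | about 45% |

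For 0.2 SD: SE = √[(0.473 × 0.527 + 0.394 × 0.606) / 120] = 0.064. The apparent reduction of 0.079 is 1.23 SE, and Φ(1.23 − 1.96) is about 0.23.

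Assuming instead direct falls of 5, 10 or 15 percentage points, the chance of a significant result favouring iCBT is about 12%, 35% or 66%, against a nominal 2.5% in that direction. The answer follows the assumption chosen.

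**The case against.** **Some masking may exist that the article does not show.** Both arms use the app for the 6-week assessment and both receive educational content, so control women are not without contact, and the consent text is not available. This is a reason to let the authors describe the masking if there is any. It does not rescue the sentence: the article affirms participant blinding while describing arms that rule it out, which is a wrong statement rather than a detail left to the full protocol.

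**The percentages above might be read as the size of this error.** They are not. The shifts are assumed. The 47.3% comes from a previous face-to-face trial whose instrument and cut-off are not given here, and the article does not say which PHQ-9 cut-off defines prevalence. Any inflation belongs to an open design with a self-rated outcome and is the same whether or not the sentence is corrected. This objection stands in full.

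**A reader might infer that any benefit seen would be spurious.** The document does not support that. The comparison is openly with usual care, and therapist contact is a declared part of iCBT, so improvement that comes from contact is partly an effect of the package under test. Reporting that changes only because the woman knows her arm is the spurious part, and its size is unknown.

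**A reader might also infer that the score reviewer is blinded, or that the trial is registered as single-blind.** The article says only that the reviewer has no other trial activities. It does not use the term single-blind, and the registry record is not shown. Neither inference is supported.

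**Unblinded psychotherapy trials are normal.** Agreed. The point asks for an accurate statement, not a different design.

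**Conclusion.** The blinding sentence is wrong as written. It claims participant blinding that is incompatible with the enrolment, intervention and control sections, for a trial whose primary outcome is rated by those same participants. This rests on reading the sections together and on no numerical assumption.

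Its consequence is for interpretation: the protocol credits the primary comparison with a protection against bias that it lacks. Sample size, power, significance level, randomization and the planned analysis are unaffected. How much bias there will be cannot be determined from the document.

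**What to change.** 1. In Randomization and blinding, replace the closing clause about participants with a statement that neither participants nor therapists are blinded and that the primary outcome is self-rated by unblinded participants. If some masking was intended, state exactly what is masked and how.
2. Limit the blinding claim to the biostatistician. Include the score reviewer only if that person is confirmed to be unaware of allocation.
3. Extend the self-report limitation in the abstract's Discussion: the contrast with usual care may include reporting bias and expectation effects from knowledge of allocation, and therapist contact is part of the package tested.
4. If a numerical illustration is used, label it as an assumption about open designs with self-report.

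The cost is a few sentences and a slightly less favourable account of the trial's rigour. No change to sample size, power or conduct is needed.

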#### Intervention

The iCBT intervention will be provided via personal devices connected to the internet or mobile network. A perinatal mental healthcare app has been designed for participants to receive text or video-based psychoeducational modules published weekly for 7 weeks by a trained therapist (Fig. 2). Three modules will be delivered antenatally, and four will be provided postnatally available until 5 weeks after delivery. Weekly modules include psychoeducation, self-monitoring logs and outcome monitoring. Written feedback from participants to the therapist via the app is also required after each module is published. Consistent with well-established CBT theory and protocols [36, 37], the main component of iCBT includes mental health education, cognitive reconstruction, problem solving strategies, behavior reinforcement, and relapse prevention. Table 1 shows the schedule of seven-week period iCBT intervention. The app records metrics that can be used to evaluate adherence or engagement, including completion of modules and recording logs, and duration of time spent in the online system. The study team will have access to the weekly activity logs and be aware of adherence to online modules. Participants will receive an automatic reminder message via the app as well as personal contact from the therapist if they have not engaged with the weekly module material or provided feedback.

**Fig. 2 Fig2:**
[figure not shown]
An example of the mobile app providing perinatal mental healthcare. **A** The registration page to sign up. **B** The contents page of providing iCBT treatment during pregnancy. **C** The contents page of providing iCBT treatment during postpartum period

**Table 1 Tab1:** Schedule of ICBT courses

Modules	Time arrangement	Content	Assignment for participants
**During pregnancy**			
Mental health education	The next day after enrolment	Education on pregnancy and mental health, including the impact of pregnancy on maternal mental health and the concept of CBT	Self-evaluation and goal setting
Behavioral activation	The second week after enrolment	Concept of negative behavior, avoidance behavior and procrastination. The use of positive or negative reinforcement	Record positive or negative behavior and make a list of behavior which should be reinforced. Set up a reward system for carrying out a mission
Cognitive restructuring	The third week after enrolment	Relationship between negative automatic thoughts and depression and anxiety. Awareness of cognitive bias and problem solving strategies	Make a list of personal typical negative automatic thoughts and record automatic thoughts within the past week. Find out negative proposals and selective thinking patterns
